## Abstract

**Background:**

Globally, approximately 55 million people are living with dementia. Osteoarthritis occurs in half of all older adults and is associated with pain, depression, and increased dementia risk. Currently, no program exists for people with osteoarthritis and cognitive decline that addresses modifiable risk factors, such as physical inactivity and lifestyle behaviors.

**Objective:**

This study aims to examine the feasibility, acceptability, and health outcomes following the 12-week Healthy Body and Mind Program, designed for people with osteoarthritis who are experiencing cognitive decline. The findings will inform the designs of larger trials.

**Methods:**

In total, 20 consenting participants aged 45 years or older with osteoarthritis and cognitive decline will be randomly allocated to the 12-week program or a waitlist control group. Feasibility and acceptability will be assessed based on retention and adherence rates to the program, the number of people who provide consent to take part in the study, and evaluation questions following completion of the program. Health outcomes will include quality of life, cognition (global, attention, learning, and memory), pain, psychological health (stress, anxiety, and depression), and physical health.

**Results:**

This study has been reviewed and approved by the University of New South Wales Human Research Ethics Committee (HC230506). This project will be carried out according to the National Statement on Ethical Conduct in Human Research (2007). As of October 2025, we have enrolled 18 participants and completed their data collection. Results are expected to be published in peer-reviewed journals during the first quarter of 2026. Participant confidentiality will be maintained in line with ethical considerations.

**Conclusions:**

This protocol reports methods to determine feasibility, acceptability, and preliminary health outcome data of the Healthy Body and Mind Program informed by individuals with lived experience of dementia and osteoarthritis.

**Trial Registration:**

ClinicalTrials.gov NCT06070818; clinicaltrials.gov/study/NCT06070818

**International Registered Report Identifier (IRRID):**

DERR1-10.2196/75816

## Introduction

### Background

Globally, approximately 55 million people are living with dementia [1]. Osteoarthritis is experienced by approximately 528 million people worldwide [2] and is associated with a 20% to 25% increase in dementia risk [3,4]. The prevalence of osteoarthritis has been reported in almost half of people living with dementia [5,6]. Both dementia and osteoarthritis are associated with increased pain and depression [7-9] and reduced quality of life (QoL) [8,10]. Comorbid conditions, such as osteoarthritis, depression, and dementia, exacerbate symptoms of a disease; for example, a higher number of comorbidities (ie, multimorbidity) correlates with more severe pain and depression [1].

Depression, anxiety, and reduced QoL are common in dementia [9,11] and osteoarthritis [12], in addition to pain [7]. Furthermore, osteoarthritis has been associated with a 1.2- to 1.5-fold increase in dementia risk [13] and rises to 5.7-fold when experienced with an additional chronic condition [14]. However, most older adults, including people experiencing cognitive decline, are living with comorbid conditions such as osteoarthritis [15,16]. Depression and anxiety are also commonly found as comorbid conditions along with cognitive decline [17] and osteoarthritis, and depression has also been linked with increased dementia risk [18].

Nonpharmacological lifestyle approaches involving physical activity (PA) have been shown to improve health outcomes for 26 different chronic conditions [19], including dementia [20] and osteoarthritis [7]. Osteoarthritis and other chronic conditions are associated with increased dementia risk [20,21], and PA and other nonpharmacological approaches improve health outcomes in older adults while reducing dementia risk [20]. PA interventions improve cognition in people living with dementia [22] as well as reduce dementia risk in older adults [20]. Studies have shown that PA and lifestyle approaches reduce dementia risk [14,20,23] and improve cognition and QoL for people already experiencing cognitive decline [24-26]. Furthermore, nonpharmacological approaches have been shown to be cost-effective [27] and preferable to pharmacological approaches for people living with dementia and their families and care partners [28].

Systematic reviews have shown that PA has a positive effect on cognition [29], depression, and QoL [30]. However, findings are inconsistent regarding the most effective type of PA. Multimodal and mind- and body-focused approaches tend to outperform singular or unimodal approaches [30]. Interventions shown to be effective in reducing pain in osteoarthritis include aerobic and strengthening exercises and multimodal approaches that incorporate lifestyle education specific to osteoarthritis, such as pain coping skills training [31]. Multimodal approaches have been shown to be more effective than unimodal approaches in reducing pain [7] and improving depressive symptoms. PA has positive effects on mental health [32] and improves outcomes for older adults living with anxiety and depression. Meta-analyses have shown that nonpharmacological approaches reduce symptoms of depression in people with cognitive decline [9] and osteoarthritis [7]. Nonpharmacological approaches include care staff education and reminiscence therapy for people living with dementia and multimodal exercise approaches (eg, combined strength, balance, aerobic, and mind-focused approaches such as tai chi and yoga) for people with osteoarthritis.

Despite this evidence, there is a lack of accessible, implementable, and scalable lifestyle programs for people living with comorbid conditions, such as cognitive decline and osteoarthritis. This gap reflects a major opportunity for improving health outcomes and reducing dementia risk. Guidelines for multidisciplinary approaches that include PA have been developed for people living with cognitive decline [33,34], but effective interventions are specifically needed to target people living with comorbidity [15,35] and reduce dementia risk. It is vital to consider associations between conditions and how symptoms may be exacerbated (eg, symptoms of depression resulting from limitations in completing usual daily activities due to osteoarthritis-related pain and cognitive difficulties).

### Objectives

We will pilot the evidence-based Healthy Body and Mind Program (HBMP), which includes PA, nutrition, lifestyle, and behavior change education on health outcomes in people living with cognitive decline and osteoarthritis. The evidence base for development of the program is outlined in Figure 1. The primary aims of this pilot randomized controlled trial (RCT) are to determine (1) the feasibility (ie, recruitment, retention, and adherence) of the HBMP for people living with osteoarthritis and cognitive decline in a community clinic and the University of New South Wales (UNSW) Medicine and Health Lifestyle Clinic, Sydney, Australia, and (2) the acceptability of the program to people living with osteoarthritis and experiencing cognitive decline. The secondary aim is to obtain pilot data on health outcomes in people with osteoarthritis and cognitive decline, following the program when compared to usual care. Health outcomes are QoL, cognition, pain, psychological health (depression, anxiety, and stress), and physical health (weight, waist circumference, blood pressure, cardiorespiratory fitness, strength, mobility, and balance). We hypothesize that individuals who complete the program will have better health outcomes when compared to the baseline and the control groups.

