### Recruitment

A total of 20 participants with osteoarthritis and cognitive decline will be recruited through the UNSW Medicine and Health Lifestyle Clinic, StepUp for Dementia Research, and general practitioner and health district referrals. Study advertisements will also be displayed electronically via online social media platforms (eg, X, formerly known as Twitter [X Corp]; Facebook [Meta Platforms, Inc]; and LinkedIn [LinkedIn Corporation]). Initial contact will be made by potential participants emailing the study investigators through the study email or the StepUp team or by referral from a health professional. A member of the research team will then contact potential participants. Participants will be screened in person, online, or over the telephone to confirm their eligibility. The lead investigator will review participant screening data and confirm participant eligibility before providing the participant information sheet and consent form (Multimedia Appendix 3). If eligible and after written consent has been obtained, potential participants will be invited to an in-person screening visit. Demographic information, chronic disease history, lifestyle behaviors, and medication use will be documented. Potential participants will complete the Adult Pre-Exercise Screening System and Exercise and Sports Science Australia [42] screening questionnaires for exercise-induced symptoms (eg, chest pain and musculoskeletal pain; Multimedia Appendix 4). To ensure safety, only people cleared through the screening will be enrolled and randomized. Once deemed eligible, participants will complete written informed consent, and baseline testing will commence. Participants will be assigned a unique ID number to ensure personal details are not linked to collected data.

Due to ethical considerations where many potential participants may not be aware of cognitive decline, the term “thinking difficulties” will be used throughout study advertisements and participant information sheets. An ethically approved protocol is in place for advising people of their health assessment results (eg, cognition and depression) and referring them to their general practitioner where appropriate. Eligible participants will have mild cognitive impairment; therefore, they will have the capacity to provide informed consent.

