### Data Collection and Outcome Measures

#### Feasibility and Acceptability

The feasibility of the program will be determined by the number of eligible participants who provide consent and retention and adherence to the program (ie, number of exercise and education sessions attended, completed, and engaged with). Retention will be determined by the percentage of participants who provide consent and complete the program. Adherence will be determined by the percentage of program sessions attended by participants who enter the program. Adherence will be recorded using attendance records (recorded by the AEP and health psychologist facilitating the sessions). The acceptability of the program will be assessed by postprogram evaluation questionnaires after the program is completed.

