### Adverse Events

PA may cause concern in older adults and people living with chronic conditions. Adverse events may occur (eg, a fall), despite the safety protocols we have put in place (eg, AEP or RA closely monitoring participants during exercise in a purposefully designed clinic or laboratory setting with handrails). Throughout the trial and follow-up, adverse events will be documented, and risk will be continually assessed by appropriately trained professionals (ie, AEP). Reported adverse events will include details about the type of event, date, time, and duration; severity (mild to severe); whether it could have been avoided; outcome (solved to fatal); and whether it was related to the study (certainly, probably, possibly, unlikely, or cannot say). The relevant ethics committee and participant’s general practitioner will be informed about any serious event (eg, requiring hospitalization) that takes place during the study. Adverse events will be reported transparently alongside study outcomes. In accordance with the CONSORT (Consolidated Standards of Reporting Trials) statement [48] and similar to other studies [53], data from participants who are suspended from the trial due to an adverse event will be entered into the analysis by their allocated treatment group. The lead researcher will continue to communicate and support the participant and signpost them to relevant support services where appropriate. An independent safety monitoring process has been established (the data safety monitoring board) to oversee participant safety and review this trial. These arrangements have been documented in a safety monitoring plan, reviewed and approved by the human research ethics committee. All research staff involved in this trial have completed training and certification in Good Clinical Practice guidelines.

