### Statistical Analysis and Clinical Interpretation

Feasibility, acceptability, and preliminary efficacy of the program will be analyzed. Feasibility will be examined by assessing group session attendance, quantified as total sessions attended out of a maximum possible and reported as a percentage. Feasibility will be quantified as session compliance with criteria for success, requiring performance of at least 10 minutes of aerobic training and 5 progressive resistance training exercises per session. Participant attendance, exercise programming, and adverse events will be recorded. Reasons for nonattendance will be collected and reported. Adverse events will be recorded, and ongoing monitoring and reporting will be completed in accordance with CONSORT guidelines [48]. Acceptability will be determined by participants’ perspectives and experiences of the program based on final participant feedback (focus groups or interviews). Acceptability will encompass what participants liked most and least about the program and their suggestions for the content and format of the sessions. Preliminary efficacy of the program will involve analysis of health outcomes (QoL, cognition, and psychological health). Quantitative data will be analyzed using SPSS Statistics (version 30.0.0.0, 172), with normality checks and descriptive statistics for frequencies and distributions. Baseline data will be compared between control and intervention groups to ensure there are no significant differences between groups at baseline. Health outcomes will be compared pre- and postprogram completion and between the intervention and control groups using 1-tailed *t* tests and repeated measures ANOVAs. Statistical significance will be set to *P*<.05. Effect sizes will be calculated using Cohen *d* for *t* tests and ηp^2^ for ANOVAs. Results will be reported comparing the intervention versus the waitlist control group and before versus after the 12-week program. Qualitative data will be analyzed using thematic content analysis [47].

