## Discussion

### Anticipated Findings

This is a pilot RCT with complementary quantitative and qualitative components that aims to determine the feasibility and acceptability of a 12-week HBMP. Furthermore, we will examine whether the program improves QoL, cognition, and other health outcomes (pain, depression, and physical health) in people with osteoarthritis and cognitive decline. Currently, there is no program available to meet the specific needs of this population, despite the prevalence of dementia rapidly increasing and the fact that half of older adults globally are living with chronic pain, often attributable to osteoarthritis. The program has been developed in partnership with people with lived experience of dementia and osteoarthritis, AEPs, clinical researchers, chronic disease specialists, and accredited practicing dietitians. The program will continue to be codeveloped, ensuring it is feasible in a real-world setting and easily scalable.

The anticipated findings of this study are that the 12-week program will be feasible and acceptable for people living with osteoarthritis and thinking concerns. Participant feedback will be valuable in informing a larger clinical trial. Regarding secondary outcome measures, we hypothesize that improvements will be observed for pain, QoL, physical function, and cognition in those who complete the program, though these may not be significant given the small sample size.

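### The health hypothesis is framed on program completers, the retention denominator is unclear, and the acceptability questionnaire follows completion, so people who leave need one stated rule

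*Protocol article*

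**What the plan says.** All references are to the protocol article.

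- **Health outcomes.** Objectives: "We hypothesize that individuals who complete the program will have better health outcomes when compared to the baseline and the control groups". Anticipated Findings repeats the condition, expecting that "improvements will be observed for pain, QoL, physical function, and cognition in those who complete the program". Statistical Analysis and Clinical Interpretation compares outcomes before and after the program and between the two arms, and does not say who is in either comparison.
- **Allocated group.** The only such rule is under Adverse Events: "data from participants who are suspended from the trial due to an adverse event will be entered into the analysis by their allocated treatment group". Ethical Considerations and Recruitment both allow withdrawal at any time. No matching rule covers people who withdraw for other reasons.
- **Retention and adherence.** Feasibility and Acceptability: "Retention will be determined by the percentage of participants who provide consent and complete the program". Adherence has a different base: "Adherence will be determined by the percentage of program sessions attended by participants who enter the program".
- **Consent.** Recruitment first says "If eligible and after written consent has been obtained, potential participants will be invited to an in-person screening visit". Later in the same paragraph, written consent follows confirmation of eligibility and directly precedes baseline testing. Only people cleared at screening are randomised.
- **Acceptability.** Feasibility and Acceptability: "The acceptability of the program will be assessed by postprogram evaluation questionnaires after the program is completed". The abstract likewise places the evaluation questions after completion. The statistical section instead judges acceptability "based on final participant feedback (focus groups or interviews").

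**The concern.** Controls are not selected on completing anything during their 12 weeks of usual care. If intervention participants are selected on completion, the contrast is no longer the randomised one. If people who are less well or in more pain leave the program, it favours the program.

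Retention is part of the first primary aim. If its denominator can include people who failed in-person screening, or waitlist members who left before their first session, one percentage mixes screening losses, waiting losses and true program dropout. A team planning the larger trial needs these separately.

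Acceptability is the second primary aim. A questionnaire given after completion is likely to be answered mainly by those who stayed, who are the people least likely to have found the program unacceptable.

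**Working it through.** The article reports no result on these points that can be reproduced. The check compares the definitions and then sizes each effect under stated assumptions.

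**1. Completer comparison**

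Inputs: target difference 0.5 SD and attrition 15%-20%, both from Sample Size Calculation. That attrition range inflates the hypothetical full trial (85 × 1.20 = 102 per group). It is not a forecast for this pilot and is borrowed here as an assumption. The gap *g* between completers and dropouts is not documented; 0.5 to 1.0 SD is assumed.

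Suppose there is no true effect, dropout is a fraction *d* of the intervention arm only, and dropouts score *g* below completers. The mean of the whole arm is then the completer mean minus *d* × *g*, so using completers alone overstates the arm by *d* × *g*.

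| *d* | *g* (SD) | Shift (SD) | Share of 0.5 SD |
|---|---|---|---|
| 0.15 | 0.5 | 0.075 | 15% |
| 0.20 | 0.5 | 0.10 | 20% |
| 0.15 | 1.0 | 0.15 | 30% |
| 0.20 | 1.0 | 0.20 | 40% |

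For scale, the standard error of a standardised difference with 10 per arm is about √(1/10 + 1/10) = 0.45 SD.

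**2. Retention with screen failures counted**

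Inputs: 20 randomised (Recruitment). Completers are assumed to be 17 or 16, which is 15% or 20% loss. Screen failures after consent are assumed to be 0, 2, 4 or 6. Retention = completers / (20 + screen failures).

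| Screen failures | 17 completers | 16 completers |
|---|---|---|
| 0 | 17/20 = 85% | 16/20 = 80% |
| 2 | 17/22 = 77% | 16/22 = 73% |
| 4 | 17/24 = 71% | 16/24 = 67% |
| 6 | 17/26 = 65% | 16/26 = 62% |

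The choice of denominator moves the figure by about 7 to 20 percentage points. The exact 95% CI for 17/20 is 62% to 97%, so the estimate is imprecise even when its denominator is clear.

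**3. Retention with waitlist losses before the start**

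Take 20 randomised, 2 waitlist members who leave during usual care and 17 completers (assumed). Completion is 17/20 = 85% of those randomised but 17/18 = 94% of those who started. Both figures are legitimate, but they answer different questions, and the retention definition does not separate them.

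**4. Acceptability**

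No arithmetic applies. One section measures acceptability by a questionnaire after completion and another by final focus groups or interviews. Neither commits to asking people who stopped.

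**The case against.** The strongest reply is that no section restricts the efficacy analysis to completers. Objectives and Anticipated Findings state hypotheses, the statistical section compares intervention with control, and the one population rule that exists follows allocation. An analysis plan that is not shown may name the population. This stands: a reader might infer that the trial will test completers against controls, but the text does not establish it. What remains is a hypothesis worded on completers, stated twice, next to an allocation rule that covers only one reason for leaving.

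On retention, the feasibility paragraph opens with eligible people who consent, and one of the two consent statements follows eligibility, so screen failures may not be counted at all. That also stands, and it is why the two statements need reconciling. A reader might further infer that screen failures bias the randomised comparison or acceptability. They cannot, because they are never randomised and never enter the program; they could only lower retention. Nor do dropouts bias a completers-over-consenters ratio, which counts them as failures. A waitlist member who leaves early is real trial attrition, but not dropout from a program that had not begun for that person.

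On acceptability, a reader might infer that people who left are never asked. The documents do not say so. The section on lived-experience involvement invites participants and support persons to focus groups or interviews without a completion condition, and the statistical section records why sessions were missed. It is fair to say only that those who stopped are not assured of being asked.

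The size is also open to challenge. The attrition range belongs to another trial, the gap is assumed, and a 0.20 SD shift is less than half of a 0.45 SD standard error. Health outcomes are secondary, and Anticipated Findings concedes that they may not reach significance. All of this stands and limits the weight of the point.

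**Conclusion.** The concern holds as a matter of definitions to correct, not as demonstrated bias. As written, the plan allows a non-randomised completer comparison, a retention figure that may mix screening and waiting losses with program dropout, and questionnaire-based acceptability drawn from those who stayed.

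A completer comparison would be shifted by about 0.08-0.20 SD, or 15%-40% of the 0.5 SD target. This assumes one-sided dropout of 15%-20% and dropouts 0.5-1.0 SD worse. If dropouts were better off, or left both arms alike, the shift would shrink or reverse. Retention could be understated by about 7 to 20 percentage points if 2 to 6 screen failures were counted (assumed). The size of any acceptability bias cannot be derived from the document.

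The change is worth making because the findings are meant to inform larger trials, and the two main corrections use data already collected.

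**What to change.** 1. Restate the hypothesis and the between-group analysis for all randomised participants with week-12 data, by allocated group and whatever their attendance. Extend the adverse-event rule to every withdrawal. Keep completers as a supportive analysis, and report missing week-12 data by arm.
2. Reconcile the two consent statements. Report retention as randomised participants assessed at week 12, by arm, and program completion as completers over those who started, each with an exact 95% CI. Show screen failures and waitlist losses before the start separately.
3. Report acceptability with the number of starters who did and did not answer. Include those who stopped where this is still feasible, and limit the conclusion to respondents.

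**Cost.** Items 1 and 2 need wording and re-tabulation of existing data. The Results section reports 18 participants enrolled with data collection completed by October 2025, so bringing dropouts back for a week-12 visit is largely closed off and late feedback from them may not be obtainable. Reported acceptability may be less favourable. An analysis of those with week-12 data still omits dropouts who were never assessed, which is why the missing data must be shown by arm.
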